### 2.6. Allocation and Randomization 

Participants were randomly assigned into one of four intervention groups: control group (no intervention), needling group (receiving a needling intervention but not electrical current), low-intensity percutaneous electrolysis group (receiving percutaneous electrolysis with low intensity of electrical current), and high-intensity percutaneous electrolysis (receiving percutaneous electrolysis with a high intensity of electrical current). 

Concealed allocation was conducted with a computer-generated randomized table of numbers created by an external statistician not involved in the analysis or interpretation of the results. Individual and sequentially numbered index cards with random assignment were prepared. The index cards were placed in sealed opaque envelopes, which were opened by an external assessor. Treatment allocation was revealed to the participants after collection of baseline outcomes. 

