## Abstract

Percutaneous electrolysis consists of the application of a galvanic electrical current throughout an acupuncture needle. It has been previously hypothesized that needling procedures’ neurophysiological effects may be related to endogenous pain modulation (EPM). This protocol study describes the design of a double-blind (participant, assessor) randomized controlled trial with the aim to investigate whether percutaneous electrolysis is able to enhance EPM and whether the effect is different between two applications depending on the dosage of the galvanic electrical current. Seventy-two asymptomatic subjects not reporting the presence of pain symptoms the previous 6 months before the study, aged 18–40 years, are randomized into one of four groups: a control group who does not receive any intervention, a needling group who receives a needling intervention without electrical current, a low-intensity percutaneous electrolysis group (0.3 mA × 90 s), and a high-intensity percutaneous electrolysis group (three bouts of 3 mA × 3 s). Needling intervention consists of ultrasound-guided insertion of the needle on the common extensor tendon of the lateral epicondyle. The primary outcome is conditioned pain modulation (CPM), and secondary outcomes include widespread pressure pain sensitivity (pressure pain thresholds (PPT) over the lateral epicondyle, the cervical spine, and the tibialis anterior muscle) and temporal summation (TS). We expected that percutaneous electrolysis would have a greater influence on CPM than an isolated needling procedure and no intervention. In addition, we also postulated that there might be differences in outcome measures depending on the intensity of the electrical current during the percutaneous electrolysis application. This study makes a new contribution to the field of neurophysiological effects of percutaneous electrolysis and needling interventions.

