### 2.3. Interventions

This randomized clinical trial had four groups: control group who did not receive any intervention, needling group who received a needling intervention, low-intensity percutaneous electrolysis group who received the intervention for a longer period of time with low intensity of the electrical current (0.3 mA × 90 s), and high-intensity percutaneous electrolysis group who received the intervention for a shorter period of time with high-intensity electrical current (3 bouts of 3 mA × 3 s). All interventions were performed by a physical therapist with more than 10 years of experience in the technique. 

The control group did not receive any intervention for 5 min (time period similar to the remaining groups). The remaining groups received a single session of an ultrasound-guided needle intervention on the common extensor tendon of the lateral epicondyle of their dominant side. Participants were comfortable in a supine position with the dominant elbow on the table in a position of 20° flexion and with the forearm pronated. As described by Rodríguez-Huguet et al. [27], a 25 × 0.3 mm acupuncture needle (Agupunt, Barcelona, Spain) was inserted ultrasound-guided 45° to the skin towards the lateral epicondyle to reach the deep surface of the common extensor tendon. The technique of inserting the needle and the time it is embedded into the participant’s tissues were the same for all groups (90 s) for avoiding different mechanical effect of the needle. The three procedures only differed in the application or not of the electrical current and the intensity of the galvanic current that was applied through the needle. 

The needling group received just the needing intervention without the application of any electrical current. The needle was ultrasound-guided inserted into the common tendon of the lateral epicondyle and left in situ for 90 s without galvanic current. This needling procedure has been previously used in a randomized clinical trial investigating the effects of percutaneous electrolysis in people with plantar heel pain [28].

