### 2.4. Outcomes

All outcomes were evaluated before (2 min) and immediately after (2 min) the intervention by an assessor blinded to the treatment allocation group. The experiment always took place in the same quiet room with a similar temperature and schedule for all participants. Before the baseline outcomes, the following socio-demographic variables were assessed: age (years), gender (male or female), weight (kg), height (m), body mass index (BMI) (kg/m^2^), smoking (yes or no), and level of physical activity (measured by the short version of the International Physical Activity Questionnaire (IPAQ-SF)) [30]. The order of outcome assessment was always the same: widespread PPTs, CPM and TS.

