#### 2.4.1. Primary Outcome

The primary outcome was conditioned pain modulation (CPM), which was tested using the upper extremity submaximal effort tourniquet test [31]. Specifically, participants were asked to elevate their non-dominant upper extremity for one minute. A blood-pressure cuff was inflated to a pressure of 280 mm Hg. Participants rated the tourniquet-induced pain intensity of the upper extremity on an 11-point numerical pain rate scale (NPRS, 0–10). The cuff was deflated 6 min after, and 3 trials of pressure pain thresholds (PPTs) at the extensor tendon of the lateral epicondyle, cervical spine, and tibialis anterior muscle were obtained immediately following cuff deflation. Activation of CPM was operationally defined as an increase in PPTs of at least 10% following the conditioning stimulus (tourniquet test). These methods correspond to recommendations on practice of CPM testing [31].

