### 2.7. Blinding

Both participants and assessors were blinded to the participants group allocation. Due to the nature of the intervention, the clinician could not be blinded. Additionally, the statistical analysis was conducted by an independent statistician who will not aware of the intervention group. 

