### 3.2. Limitations

It should be recognized that this protocol has some limitations. First, this study will include healthy participants, which will make it difficult to extrapolate the results to daily clinical practice. Nevertheless, we consider that it is highly important to determine the physiological effects of an intervention such as percutaneous electrolysis first in healthy individuals showing proper CPM and as a second step to determine its effects in different chronic pain conditions, where CPM is usually impaired and, therefore, the response maybe different. Second, another consideration is the inclusion of a non-intervention group to determine the effects of time on CPM. Additionally, although the participants will be blinded from their group assignment, some subjects may perceive discomfort related to the application of galvanic current and identify the intervention that they receive. Successfully blinding will be confirmed by asking the participants which intervention they believed had received. It should be recognized that it will be not possible to blind the therapist who will apply the interventions, considering the treatment approach that is proposed. It would increase the risk of bias due to deviation from intended interventions. Finally, the results of this study will be restricted to the immediate effects of assessments. Since this is a mechanisms-related study, this is the common procedure in published studies [40,41,42].

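### The protocol says participants were told their allocation after baseline, which contradicts its claim of participant blinding; comparisons with the un-needled control arm cannot be participant-blind in any case

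*Protocol article*

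**What the plan says.** The Abstract of the protocol article describes a "double-blind (participant, assessor) randomized controlled trial". Section 2.7 repeats the claim: "Both participants and assessors were blinded to the participants group allocation". It adds that the treating clinician could not be blinded.

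Section 2.6, on allocation, says: "Treatment allocation was revealed to the participants after collection of baseline outcomes".

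Section 2.4 gives the assessment schedule: "All outcomes were evaluated before (2 min) and immediately after (2 min) the intervention by an assessor blinded to the treatment allocation group". No later assessment is described.

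Section 2.3 describes the arms. For control: "The control group did not receive any intervention for 5 min". No sham is described. For the needled arms: "The three procedures only differed in the application or not of the electrical current and the intensity of the galvanic current". Insertion technique and needle time (90 s) are common to all three.

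Section 3.2 says that participants will be blinded, accepts that some may feel the current and so recognise their treatment, and plans a check: "Successfully blinding will be confirmed by asking the participants which intervention they believed had received".

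**The concern.** A participant who has been told the group is not blinded, and asking that participant to guess the group tests nothing. If Section 2.6 describes what happened, the trial lacks a property that it claims in three other places.

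This matters because every outcome runs through the participant's report. A pressure pain threshold (PPT) is recorded when the participant says that pressure has become painful. Conditioned pain modulation (CPM), the primary outcome, is built on PPTs: "Activation of CPM was operationally defined as an increase in PPTs of at least 10% following the conditioning stimulus". Temporal summation (TS) is the difference between two pain ratings. Blinding the assessor does not protect against what the participant expects. Expectation could plausibly run in the hypothesised order, with current above needle alone and needle alone above nothing, and the design would then have difficulty separating it from the mechanism under study.

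The control arm raises a second problem that does not depend on Section 2.6. People who receive no needle know it, and people who receive one know that they are not controls. The primary aim in the Introduction names no intervention as a comparator beside needling, so part of the primary question is participant-unblinded by design.

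**Working it through.** The plan states no figure on this point, so the check is a comparison of the sections.

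**Step 1. Statements about participants.**

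| Section | What it implies for participants |
|---|---|
| Abstract | blinded |
| 2.7 | blinded |
| 3.2 | blinded; asked afterwards to guess their intervention |
| 2.6 | told their allocation once baseline is complete |

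Three sections agree and one contradicts them.

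**Step 2. When disclosure would fall.** Section 2.4 has two assessments, one 2 min before and one 2 min after the intervention. Section 2.6 places disclosure after the first. The second follows the intervention almost at once, so the natural order is baseline, disclosure, intervention, outcomes. Section 2.6 gives no exact moment, and the timeline figure is not available in the text at hand. The order is therefore an inference.

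**Step 3. Who could be blind under each reading.** Section 2.5 gives 18 per group in four groups, 4 × 18 = 72.

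- Section 2.6 taken literally: none of the 72 is blind at the post-intervention tests.
- Section 2.6 as a slip: the 18 controls know that they received nothing. The other 3 × 18 = 54 know that they were needled, but may be blind to which needled arm they are in, subject to the felt current that Section 3.2 concedes.

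**Step 4. Which comparisons are affected on the second reading.** Four arms give 4 × 3 / 2 = 6 pairs, of which 3 include control. The aims in the Introduction name five contrasts: each electrolysis arm against needling (2), each against no intervention (2), and low against high intensity (1). Two of these five include control. These counts show which contrasts are open to participants; they do not measure bias.

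**Step 5. How expectation could enter each outcome.** Let B and A be the PPT before and after the tourniquet within one assessment, so that the relative CPM response is (A − B)/B. If expectation multiplies both by the same factor k, the response is (kA − kB)/(kB) = (A − B)/B, which is unchanged. If it adds the same amount d to both, the absolute rise A − B is unchanged and the relative rise becomes (A − B)/(B + d). If it acts differently on the two readings, adding d₁ to B and d₂ to A, the absolute rise shifts by d₂ − d₁. A constant shift in ratings also drops out of TS, which is a 10th-minus-1st difference. Raw PPTs, a secondary outcome, have no such protection. Nothing in the document gives a value for k, d, d₁ or d₂.

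**The case against.** The strongest reply is that Section 2.6 is one sentence against three sections, and that the guess question makes sense only if participants were not told. A slip, for instance for disclosure to the therapist, is quite possible. This stands as far as it goes: a reader might infer from Section 2.6 that no arm was blinded in fact, and the document does not establish that. It also does not establish the opposite, and the contradiction remains until someone states what was done.

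A reader might also infer that the trial claims double-blinding without qualification. It does not. The Abstract specifies participant and assessor, Section 2.7 excludes the clinician, and Section 3.2 concedes that the current may be felt. The gap is narrower: nothing says that control participants cannot be blind. Nor does Section 2.6 give any ground for doubting the blinding of the outcome assessor.

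It can fairly be said that the control arm is presented in Section 3.2 as a check on change over time, and that the first hypothesis sets electrolysis against dry needling only. That limits the weight of the control contrast but does not remove it, because the primary aim still names it. Whether to demote that contrast to a supportive role is a trade-off for the investigators and is not needed to correct the plan.

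Finally, an expectation effect common to the readings before and after the tourniquet would largely cancel in CPM. That is correct. It lowers the concern for the primary outcome relative to raw PPTs, but not to zero, since expectation may act on the conditioned change itself.

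**Conclusion.** The point holds as a contradiction within the document and an omission. Section 2.6 conflicts with the Abstract, Section 2.7 and Section 3.2 on whether participants were blinded. On the natural reading, which rests on the two-assessment schedule, it places disclosure before all post-intervention CPM, PPT and TS measures. Followed as written, it removes participant blinding in all four arms and empties the guess question of meaning. Independently of that sentence, comparisons with the no-intervention arm cannot be participant-blind, and the limitations do not acknowledge this.

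The size of any bias cannot be derived from the document, and none is claimed. The sample size arithmetic is not affected.

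**What to change.** First establish what participants were actually told and when, then reconcile Sections 2.6, 2.7 and 3.2. Much of the article is in the past tense and the limitations are in the future tense, so the text alone does not show whether this can still be changed or only reported.

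- **If participants were not told:** correct Section 2.6 to say that allocation was disclosed after baseline only to those delivering the intervention, and withheld from participants until after the last post-intervention test and the guess question. State the part played by the external person who opens the envelopes.
- **If they were told:** withdraw the participant-blinding claim and drop the guess question as evidence of blinding. Rewording Section 2.6 would not repair this case.
- **In either case:** confine any participant-blinding claim, and the analysis of the guess question, to the three needled arms. Report comparisons with no intervention as participant-unblinded, and say so in Section 3.2.

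No extra participants or staff are needed. The cost is a weaker blinding claim for the control contrast and, if participants were told, loss of the claim altogether.

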### 2.7. Blinding

Both participants and assessors were blinded to the participants group allocation. Due to the nature of the intervention, the clinician could not be blinded. Additionally, the statistical analysis was conducted by an independent statistician who will not aware of the intervention group. 

### 2.8. Statistical Methods 

Data were analyzed by using the IBM-SPSS software package (version 26.0). The significance threshold was established at 0.05 and the limits of the confidence interval at 95%. Changes in outcomes were tested on the basis of the intention-to-treat principle. Firstly, the distribution of normality for all the variables was checked by the Shapiro–Wilk test. Then, a descriptive analysis of baseline characteristics of the sample was reported, calculating the means and standard deviations for those variables with normal distribution and the median and interquartile range for those with non-normal distribution.

Subsequently, to assess the effects of the interventions, we conducted repeated measures analysis of variance (ANOVA) tests for quantitative variables (or Kruskal–Wallis test for non-normal variables) and the Bonferroni test as post hoc comparisons. Mixed-effect regression models considering the group effect, time effect, and group x time interaction were conducted. 

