#### 2.4.2. Secondary Outcome

The secondary outcomes included widespread pressure pain sensitivity and temporal summation. All outcomes were assessed by using a digital pressure algometer (Force One FDIX, Wagner Instruments, Greenwich, CT, USA) with a round rubber surface of 1 cm^2^. Participants were supine. Algometry measurements were conducted at the following three locations bilaterally in the following order: common extensor tendon at the lateral epicondyle, tibialis anterior, and cervical spine. These locations were marked with a pen to assess all measurements at the same points.

Widespread pressure pain sensitivity was assessed by determining PPTs bilaterally in the treatment point (elbow), segmental-related point (cervical spine), and a distant non-related point (tibialis anterior). The pressure was applied perpendicular over each point at a rate of 1 kg/s approximately until the subject felt the first sensation of pain [32,33]. At this moment, the algometer was removed and the measurement value was recorded. Participants had two practice trials on the hand before the evaluation begins. Three measurements were obtained at each assessed point with a 30-s interval for avoiding temporal summation [34] and the mean was used for the analysis. If there was a difference of more than 1 kg/cm^2^ between two consecutive measurements at the same point, the highest value was removed and another measurement was obtained.

The evaluation of temporal summation (TS) began one minute after the end of the CPM assessment. The sequential stimulation of mechanical pressure stimuli consisted of 10 pressures with the algometer at PPT level (with 1-s interval between them) on each of the three assessed points, i.e., elbow, neck, and tibialis anterior [35]. The subjects were asked for rating their pain of the 1st and 10th pulse on a numerical pain rating scale (NPRS; 0 = no pain, 10 = maximum tolerable pain). The final rating of TS resulted from the difference between the 10th and the 1st pain rating scores [36]. Figure 1 graphs the experimental protocol timeline.

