### 2.5. Sample Size 

The sample size was calculated for the primary outcome. Overall, an increase of at least 10% in PPTs following the conditioning stimulus was considered as an activation of CPM [31]. The determinations were based on detecting pre-post differences of 20% on PPTs following the conditioning stimulus with an alpha level of 0.05, and a desired power of 80%. This generated a sample size of at least 16 participants per group. Similarly, we calculated sample size according to clinically relevant changes. We estimated a large effect size of 1.05 (Cohen’s d) for changes in PPTs following the conditioning stimulus with a statistical power of 80% and an alpha error of 0.05. Therefore, we estimated 16 subjects per group, and considering a 10% lost, 18 individuals per group were recruited (72 subjects in total). GPower 3.1 program was used to calculate the sample size [37].

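### A Shapiro–Wilk pretest decides between repeated-measures ANOVA and a Kruskal–Wallis test that is not like-for-like, and neither the fallback's input nor the deciding analysis is fixed

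*Protocol article*

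**What the plan says.** All of the analysis text is in section 2.8 of the protocol article.

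- **Trigger.** "the distribution of normality for all the variables was checked by the Shapiro–Wilk test".
- **Main test and fallback.** Effects are assessed by "repeated measures analysis of variance (ANOVA) tests for quantitative variables (or Kruskal–Wallis test for non-normal variables", followed by Bonferroni post hoc comparisons.
- **Further model.** "Mixed-effect regression models considering the group effect, time effect, and group x time interaction were conducted". No normality condition is attached to it, and it is not ranked against the ANOVA or Kruskal–Wallis result.
- **General statement.** "Changes in outcomes were tested on the basis of the intention-to-treat principle".

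Section 2.4 gives two time points: "All outcomes were evaluated before (2 min) and immediately after (2 min) the intervention". The primary aim in section 1 compares the effect of percutaneous electrolysis on endogenous pain modulation with needling alone and with no intervention. With pre and post measurements, this asks whether the change differs between groups.

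For temporal summation (TS), section 2.4.2 says: "The final rating of TS resulted from the difference between the 10th and the 1st pain rating scores". Each rating is on a 0–10 scale.

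**The concern.** Repeated-measures ANOVA carries group, time and their interaction. Kruskal–Wallis compares independent groups on one value per participant. Putting it in the place of the ANOVA leaves open which value that is, and the hypothesis depends on the answer.

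The switch also rests on the distribution of the variables, whereas the model's assumption concerns its residuals. A pooled variable can look non-normal simply because the arms differ. TS is a difference of two whole-number-type ratings, so its discreteness alone may trip the test.

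The risk is that the question answered for an outcome, or for one of the three measurement sites (elbow, neck, tibialis anterior), is settled by a noisy pretest. The mixed model could then give a different answer, with nothing to say which one counts.

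**Working it through.** **1. The plan's own figure.** Section 2.5 states "We estimated a large effect size of 1.05" (Cohen's d), 80% power and alpha 0.05. A two-sided two-sample t test gives n = 15.26, rounded up to 16 per group (power at 16: 0.820). Allowing for 10% loss, 16/0.9 = 17.8, rounded up to 18, and 4 × 18 = 72. The stated 16, 18 and 72 reproduce, and nothing below changes them.

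**2. What Kruskal–Wallis can test with two time points.** With one pre and one post value, the group-by-time F equals the one-way ANOVA F on change scores. On a simulated data set of 4 × 18, both routes gave F = 0.40602. Kruskal–Wallis on change scores is therefore the direct rank counterpart of the interaction test. Kruskal–Wallis on post values is not.

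**3. Power under each reading.** The documents give neither the pre-post correlation (rho) nor a between-arm shift in SD units for a four-arm comparison. Both are assumed here: normal data with SD 1 at each time, 16 per arm, two arms shifted by 0.8 SD, and alpha from section 2.8 ("The significance threshold was established at 0.05"). Simulated power:

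| rho | Kruskal–Wallis, post | Kruskal–Wallis, change | Group by time | ANCOVA |
|---|---|---|---|---|
| 0.3 | 71% | 56% | 59% | 78% |
| 0.5 | 71% | 72% | 74% | 85% |
| 0.7 | 73% | 92% | 93% | 96% |
| 0.85 | 71% | 100% | 100% | 100% |

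**4. Analytic cross-check.** The arm means are 0, 0, 0.8 and 0.8, each 0.4 from the grand mean. The noncentrality is λ = 16 × 4 × 0.4² / σ² = 10.24/σ².

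- Change scores: σ² = 2(1 − rho) = 1.4, 1.0, 0.6, 0.3, so λ = 7.31, 10.24, 17.07, 34.13. The noncentral F (3 and 60 df) gives power 58/74/93/100%.
- ANCOVA: σ² = 1 − rho² = 0.91, 0.75, 0.51, 0.2775, so λ = 11.25, 13.65, 20.08, 36.90. The noncentral F (3 and 59 df) gives power 78/86/97/100%. This leaves out the small cost of estimating the slope.

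Both agree with the simulation to within about one point. Since 1 − rho² = (1 − rho)(1 + rho) is less than 2(1 − rho) whenever rho < 1, ANCOVA has the smaller error variance at every rho shown.

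**5. A smaller effect.** With 4 × 18 and a 0.5 SD shift, power for group by time / Kruskal–Wallis on change / Kruskal–Wallis on post is:

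- rho 0.3: 27/24/37%
- rho 0.5: 39/36/36%
- rho 0.7: 61/57/35%
- rho 0.85: 91/89/36%

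The pattern is the same.

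**6. Different questions.** Take a fixed 0.5 SD baseline difference in one arm, no differential change, and rho 0.8. Rejection rates are 5.5% for group by time, 5.7% for Kruskal–Wallis on change and 27.5% for Kruskal–Wallis on post. This does not show an inflated type I error under randomisation: with no group difference at either time, the post-value test rejected in 4–5% of runs. It shows that a given data set can yield opposite answers depending on the input chosen.

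**7. The pretest.** A truly normal variable is switched 5% of the time. For six independent normal variables, the chance of at least one switch is 1 − 0.95⁶ = 26% (illustrative). For TS, a simulation of whole-number ratings rounded from normal data, under four assumed rating distributions, had Shapiro–Wilk reject in 29–71% of samples of 18 and in 99–100% of samples of 72.

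**The case against.** Several stronger readings are tempting, and the documents do not support them.

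- **That Kruskal–Wallis cannot test the group-by-time effect.** With two time points it can, if run on change scores. In the table this costs at most 3 percentage points against the interaction test. For skewed (lognormal) data at rho 0.8 with a 0.5 SD shift it gains: 75% against 69%.
- **That the fallback ignores baseline.** This is one reading. The same section speaks of testing changes, so change scores are a natural reading too. However, that sentence introduces the intention-to-treat principle and does not define what enters the rank test.
- **That the interaction is lost for non-normal outcomes.** The mixed models carry it for every outcome, whatever Shapiro–Wilk shows. What is missing is a rule for which result decides.
- **That post-value analysis always loses power.** It does not. At rho 0.5 it is about level with the interaction test, and at 0.3 it does better (71% against 59%).
- **That a false switch is near certain.** Counting 24 checks (4 arms × 2 times × 3 sites) gives 1 − 0.95²⁴ = 71%, but the protocol specifies no such layout, and the checks would not be independent.

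It is also fair to say that an article may leave detail to a fuller plan, so the unspecified input alone would be a weak point. But the article itself states the switch, and names a fallback that does not match the test it replaces. That part stands.

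**Conclusion.** The point holds as a defect in how the analysis is fixed; it does not show that the group-by-time question goes unanswered. The stated procedure lets a pretest on the variables choose between two tests that are equivalent in aim only under one reading of the fallback. It then adds a third analysis without ranking it.

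The size depends on that reading and on the unknown rho. If the fallback uses change scores, the loss against group by time is 0 to 3 points in the 0.8 SD setting. If it uses post values, the result runs from a 12-point gain at rho 0.3 (71% against 59%) to a 29-point loss at rho 0.85 (71% against 100%). Baseline-adjusted ANCOVA is best or level throughout. These figures rest on the assumed shift, normal data and the range of rho shown. The wording problem does not depend on them.

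**What to change.** In section 2.8, or in the analysis plan before group codes are opened:

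1. Remove the Shapiro–Wilk switch.
2. Name one baseline-adjusted model as the deciding analysis for every outcome and site: ANCOVA on the post value with baseline as covariate, or a baseline-adjusted mixed model. On complete data with two time points, a mixed model with unrestricted group, time and group-by-time terms reproduces the change-score comparison, so the baseline adjustment must be stated.
3. Assess the residuals of that model, not the raw variables.
4. Keep any rank test as a sensitivity analysis, and state that it is run on change scores.
5. Drop the repeated-measures ANOVA or label it supportive, so that one result decides.

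The cost is analysis wording only. No extra data are needed, and the 16 per group, 18 after allowance for loss and 72 in total are unaffected.

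### The group-by-time test on one pre and one post reading is a valid change-score comparison, but adjusting for the baseline already collected would be more precise

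*Protocol article*

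**What the plan says.** Section 2.4 (Outcomes) of the protocol article sets the measurement schedule: "All outcomes were evaluated before (2 min) and immediately after (2 min) the intervention". Each participant therefore contributes one pre and one post value per outcome.

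Section 2.8 (Statistical Methods) names the analysis: "we conducted repeated measures analysis of variance (ANOVA) tests for quantitative variables (or Kruskal–Wallis test for non-normal variables) and the Bonferroni test" for post hoc comparisons, and then: "Mixed-effect regression models considering the group effect, time effect, and group x time interaction were conducted". Neither sentence lists the baseline value as a covariate, and nothing in the article constrains the group means to be equal at baseline. The rank-based fallback for non-normal variables names no baseline adjustment either.

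Section 2.6 (Allocation and Randomization) places the baseline before disclosure: "Treatment allocation was revealed to the participants after collection of baseline outcomes".

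Section 2.5 (Sample Size) sizes the trial on a change: "We estimated a large effect size of 1.05 (Cohen’s d) for changes in PPTs following the conditioning stimulus". Power is set at 80% and alpha at 0.05. This leads to 16 per group, raised to 18 for a 10% loss, and 72 in total.

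**The concern.** A model with free group, time and group-by-time terms, fitted to two readings per person, tests the treatment through the interaction. That interaction is the between-group difference in mean change. It subtracts the whole baseline reading, noise included, whatever the correlation between the two readings. Regressing the post value on the baseline subtracts only the part that predicts the post value, and so leaves less residual variance.

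At stake is precision in a trial planned on 16 analysable participants per group, with a second hypothesis that separates the two current intensities. The primary outcome, conditioned pain modulation (CPM), is itself derived from pressure pain thresholds (PPTs) before and after a tourniquet. It may therefore have a lower pre-post correlation than a raw threshold, and a low correlation is where a change score loses most. This is plausible, but the article gives no reliability figure to confirm it.

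**Working it through.** **Inputs from the article.** One pre and one post reading (section 2.4). Model terms group, time and group by time (section 2.8). d = 1.05, alpha 0.05, power 80%, 16 per group, 10% loss, 18 per group, 72 in total (section 2.5). Four groups (section 2.3).

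**Assumptions.** The pre-post correlation r is not stated, so a range from 0.3 to 0.9 is shown. Pre and post variances are taken as equal. The value d = 1.05 is read as a between-group difference in standard deviations of the change.

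**1. The plan's own figure.** A two-sided two-sample t-test (noncentral t) with d = 1.05, alpha 0.05 and 80% power needs n = 15.26, so 16 per group, where power is 82.0%. Allowing for loss, 16/0.90 = 17.8, so 18, and 4 × 18 = 72. The stated figures reproduce.

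**2. Equivalence.** On one simulated data set of four arms of 16, the repeated-measures interaction F was 6.4489 and the one-way ANOVA F on change scores was 6.4489. The mixed-model interaction coefficient and standard error (1.1676, 0.2999) matched those of the change-score regression (1.1676, 0.2999).

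**3. Variance.** With common variance σ²:
- change score: 2σ²(1−r)
- ANCOVA: σ²(1−r²) = σ²(1−r)(1+r)
- ratio: (1+r)/2

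The standard error shrinks by 1 − √[(1+r)/2]. An effect of 1.05 on the change scale becomes 1.05/√[(1+r)/2] on the ANCOVA residual scale. At r = 0.3, for example, √0.65 = 0.806 and 1.05/0.806 = 1.302.

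**4. Results** for one two-group contrast at two-sided 0.05, without Bonferroni correction. Change-score power is 82.0% at 16 per arm and 86.4% at 18 per arm.

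| r | Variance ratio | SE reduction | Effective d | ANCOVA power, 16 per arm | ANCOVA power, 18 per arm | n per arm for 80% power |
|---|---|---|---|---|---|---|
| 0.3 | 0.65 | 19.4% | 1.302 | 94.6% | 96.7% | 11 |
| 0.5 | 0.75 | 13.4% | 1.212 | 91.3% | 94.2% | 12 |
| 0.7 | 0.85 | 7.8% | 1.139 | 87.6% | 91.3% | 14 |
| 0.9 | 0.95 | 2.5% | 1.077 | 83.8% | 88.1% | 15 |

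**5. Check by simulation** (6000 runs per r, 16 per arm, error pooled over four arms, covariate fitted). Power for change score and ANCOVA was 83% and 95% at r = 0.3, 83% and 91% at 0.5, 83% and 88% at 0.7, and 83% and 84% at 0.9.

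**6. Cost of the covariate.** Error degrees of freedom fall from 60 to 59 at 16 per arm, and estimating the slope inflates the variance by a factor of about 1.017. Setting 1.017 × (1+r)/2 = 1 gives r of about 0.97. Below that value ANCOVA has the smaller variance.

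**The case against.** The strongest reply is that nothing here is wrong. Under randomisation the change-score contrast is unbiased and keeps its type I error. The trial was sized on changes, so the sizing and the test agree. This stands, and it limits the point to efficiency.

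The gain may also be small. Both readings come from one session, minutes apart, at marked sites, and each PPT is a mean of three trials. For the threshold outcomes a high r is plausible, and at r = 0.9 the benefit is one or two percentage points of power. If both electrolysis arms shift by d = 1.05 on the change scale, the overall 3-df test already has 94% power with change scores. ANCOVA gives 99%, 98%, 97% and 95% at r = 0.3, 0.5, 0.7 and 0.9. Also, 16 per group is the number left after the planned loss; 18 are recruited.

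A reader might infer more than the article supports in four ways:
- **Bias from regression to the mean.** Chance baseline imbalance can affect a single realised trial of this size, but it does not bias the randomised comparison.
- **Misuse of the group main effect.** That term averages in a pre-treatment reading and is not a treatment effect. Section 2.8 merely lists it beside the interaction and never says that it will be read as one.
- **A larger loss of power.** Assuming +0.8 SD in both electrolysis arms and r = 0.3 gives 58% against 76% on the 3-df test. The article contains no such effect; its own figure is d = 1.05 for changes.
- **A gain for every form of CPM.** Section 2.4.1 defines CPM activation as a PPT rise of at least 10%. Neither the ratio (1+r)/2 nor ANCOVA applies to that yes/no status.

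It could finally be said that the model is a detail for an unseen analysis plan. That does not stand, because section 2.8 states the model terms itself.

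**Conclusion.** The point holds as a gain in precision, not as an error, a contradiction or a bias. With complete data the planned group-by-time test is a change-score comparison, and baseline adjustment would be more precise at any r up to about 0.97. On the article's d = 1.05, two-group power at 16 per arm rises from 82% to between 84% (r = 0.9) and 95% (r = 0.3).

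This rests on the assumed range of r, on equal pre and post variances, on reading d on the change scale, and on a continuous outcome. With unequal variances the exact ratio changes, but ANCOVA remains no less precise in large samples. With missing post values the mixed model is no longer identical to the change-score test; the planned loss is only 10%.

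**What to change.** In section 2.8, name as the deciding analysis of each continuous outcome an ANCOVA of the post-intervention value on group and the baseline value of the same outcome. A mixed model with baseline means constrained equal across groups would serve equally. For CPM, use the continuous change in PPT after the tourniquet, with its pre-intervention value as the covariate, and not the 10% responder status. Report adjusted between-group differences with 95% confidence intervals, and keep the group-by-time model as a sensitivity analysis.

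This needs no new data, visits or participants, and costs about one error degree of freedom. Much of the article is in the past tense, so timing matters: the change must be specified and dated before any unblinded analysis. Otherwise it is post hoc.
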